# Summary

Recent studies from Africa have shown that Bacillus Calmette-Guérin (BCG) vaccination is associated not only with specific protection against tuberculosis, but also with so-called non-specific beneficial effects. We recently initiated a large randomised trial of BCG vaccination in Denmark to test the hypothesis that BCG vaccination at birth has beneficial nonspecific effects on child health in Denmark. No less than 4,300 infants born at Rigshospitalet, Hvidovre Hospital and Kolding Sygehus will be randomised to BCG at birth or no vaccine (control group). Follow-up will continue until the children are 13 months of age (22 months for premature infants born before 37 weeks of gestation). Data will be collected using structured telephone interviews and clinical examinations at age 3 and 13 months.

This is a non-inferiority sub-study aiming to examine whether BCG immunisation at birth affects child development.

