# Background

As one of the most used vaccines globally, Bacillus Calmette Guérin (BCG) vaccine is administered in > 100 countries to infants at birth to decrease the incidence of severe tuberculosis. Due to the low incidence of tuberculosis in Denmark, the BCG vaccine was withdrawn from the Danish Child Immunisation Programme in 1982. Recently, studies from West Africa have shown positive non-specific effects of early BCG immunisation on childhood morbidity and mortality (1-10). The studies suggest that BCG immunisation protects against various infectious diseases, such as pneumonia, diarrhoea, meningitis and respiratory syncytial virus (7, 11). Danish children below one year of age have high morbidity, primarily from infectious diseases, and resulting increasing use of primary care services and medication (12). Our group therefore initiated a randomised trial of BCG vaccination with the overall aim to test the hypothesis that the BCG-vaccine has positive nonspecific effects in Danish children.

It may be hypothesised that if BCG immunisation at birth results in a lower burden of disease from infections and less use of medicines, BCG immunised children may have better psychomotor development. To our knowledge it has not previously been addressed whether BCG immunisation at birth affects development. In theory, BCG immunisation at birth may also result in a low grade inflammation that may affect the brain negatively, so assessing this outcome will also address an important safety issue. The overall hypothesis of this sub-study is a non-inferiority of BCG-immunised children relating to development. Assessment of development of preterm infants is already part of the Calmette study protocol.

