# Research question

Does BCG immunisation at birth affect development in children in the first year of life?

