# Sample size considerations

The overall trial

The main trial includes 4300 children to be able to detect a 20% reduction in infant hospitalisation with 90% power and α = 0.05.

Sub-study

The entire Calmette-cohort will comprise 4300 children. Of these approximately 300 will be preterm (< 37 GA). Based on a sample size of 2000 mature children in each group, an α = 0.05, a mean ASQ score of 200 with a standard deviation (SD) of 40 this study will have a power of approximately 97% to detect a 5 points difference (effect size 0.12) between mean scores in BCG vaccinated children compared to unvaccinated children. When used for screening purposes, an ASQ score of ≥1.5 SD (approximately 60 points at age 13 months) below the mean is considered indication of developmental delay (13). The high power of this sub-study will allow meaningful exploratory subgroup analyses.

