**Statistical analysis:**

1. Regression analysis of ASQ scores with BCG, prematurity and age at follow-up as independent variables.
2. Secondary outcomes subject to post-hoc Holland correction.
3. If data are not reasonably normally distributed, we will present confidence intervals obtained by bootstrapping.

**Subgroup analyses:** Premature children, sex, BCG-immunisation within two days of birth. Subgroup analyses will be conducted in case of both statistically significant and statistically insignificant primary outcome.

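### The sub-study is declared non-inferiority, but the protocol gives no margin and no criterion for concluding it; the sizing and analysis are those of a two-sided test for a difference

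*Protocol*

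**What the plan says.** The design is named twice. The Summary says "This is a non-inferiority sub-study aiming to examine whether BCG immunisation at birth affects child development". The Background says "The overall hypothesis of this sub-study is a non-inferiority of BCG-immunised children relating to development", and it presents the outcome partly as a safety matter, because inflammation after the vaccine might harm the brain.

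The other sections point elsewhere:

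- **Research question.** It has no direction: "Does BCG immunisation at birth affect development in children in the first year of life".
- **Sample size considerations (Sub-study).** The inputs are "Based on a sample size of 2000 mature children in each group" and "an α = 0.05, a mean ASQ score of 200 with a standard deviation (SD) of 40", and the claim is "this study will have a power of approximately 97% to detect a 5 points difference (effect size 0.12". The 5 points are a difference to detect. They are not called a margin or an acceptable loss. The only other benchmark, about 60 points, is a screening threshold for an individual child.
- **Statistical analysis.** The primary analysis is a regression on BCG, prematurity and age. Confidence intervals are mentioned only as a bootstrap fallback for non-normal data, with no limit to compare them with. The primary result is characterised once: "Subgroup analyses will be conducted in case of both statistically significant and statistically insignificant primary outcome".
- **Sensitivity analyses.** Data are expected for about 85% of enrolled children. An analysis without those who departed from their allocation is listed here.

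**The concern.** A non-inferiority hypothesis is defined by its margin: the largest loss that would still be accepted. Without one there is nothing to test, and no result can confirm or refute the hypothesis. The sizing and analysis instead address whether the two means differ at all, and that answer can mislead about non-inferiority in both directions. A non-significant coefficient may be compatible with an unacceptable loss. A significant deficit may be too small to matter.

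At stake is the main conclusion of a sub-study that is partly about safety. A margin chosen after the data are seen would carry little weight. The margin also determines the sample size, so it belongs in the protocol even if a separate analysis plan exists.

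**Working it through.** **Inputs.** From Sample size considerations: SD 40, 2,000 term children per arm, α = 0.05 (sidedness not stated), difference 5. From Sensitivity analyses: 85% data, so 0.85 × 2,000 = 1,700 per arm. Margins of 3, 4 and 5 points are assumptions, because the protocol gives none. Any gain in precision from covariates is ignored.

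**Standard error.** SE = SD × √(2/n).

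- n = 2,000: 40 × √(2/2,000) = 1.265; 95% CI half-width 1.96 × 1.265 = 2.479.
- n = 1,700: 40 × √(2/1,700) = 1.372; half-width 1.96 × 1.372 = 2.689.

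**The plan's own figure.** Two-sided power = Φ(5/SE − 1.96). At 2,000 per arm this is Φ(3.953 − 1.960) = Φ(1.993) = 97.7%. With the rounded effect size (0.12 × 40 = 4.8 points) it is 96.7%. A one-sided α of 0.05 gives 99.0%, a poorer match. The stated 97% is therefore best read as an ordinary two-sided difference calculation.

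**What a non-significant result excludes.** The most negative non-significant estimate is minus one half-width, so its lower 95% limit is minus two half-widths.

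- n = 2,000: −2 × 2.479 = −4.96. This just excludes a 5-point deficit, but not one of 4 or 3 points.
- n = 1,700: −2 × 2.689 = −5.38. Estimates between −2.69 and −2.31 (that is, −5 + 2.69) are non-significant, yet their lower limit is below −5.

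**What a significant result implies.** At 2,000 per arm an observed deficit of 2.5 points has a 95% CI of −2.5 ± 2.479, or −4.98 to −0.02. It is significant, yet it lies wholly within a 5-point margin.

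**Chance of a non-significant result at a true 5-point deficit.** This is 1 − power.

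- n = 2,000: 1 − 0.977 = 2.3%.
- n = 1,700: Φ(3.644 − 1.960) = 95.4%, so 4.6%.

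A confidence-limit rule with a 5-point margin would wrongly conclude non-inferiority 2.5% of the time at that deficit.

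**Non-inferiority power.** Power = Φ(margin/SE − 1.96), with one-sided α 0.025 and no true difference.

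| Margin | 2,000 per arm | 1,700 per arm | n per arm for 90% |
|---|---|---|---|
| 5 | 97.7% | 95.4% | 1,345 |
| 4 | 88.5% | 83.0% | 2,102 |
| 3 | 66.0% | 59.0% | 3,736 |

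If BCG children truly score 1 point lower, power for margin 5 at 1,700 per arm is Φ((5 − 1)/1.372 − 1.96) = 83.0%.

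**The case against.** The best defence is that the label is loose but the plan is sound. The research question is non-directional, the Background raises both benefit and harm, and a two-sided comparison answers such a question. The trial is also large enough that, at 2,000 per arm, a non-significant result would exclude a 5-point deficit anyway. Both statements are true. The first supports an alternative repair, which is to drop the label. The second depends on complete data, which the protocol does not expect, and on 5 points being the right margin, which it does not say.

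Three stronger readings are tempting, and the document does not support them.

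- **That p > 0.05 will be taken as proof of no harm.** A reader might infer this from the significant/insignificant wording. That sentence only says that subgroup analyses go ahead either way. What can be shown is that no criterion is stated.
- **That the risk of missing harm is uncontrolled.** At 1,700 per arm, true deficits of 2.5 or 3 points would be non-significant 55% or 41% of the time. Under a 5-point margin, however, those deficits are non-inferior, so these figures show no error. In one sex alone (about 850 per arm if evenly split), a 5-point deficit would be non-significant 27% of the time, but the protocol makes no non-inferiority claim within each sex.
- **That non-adherence invalidates the main comparison.** Departures from allocation could dilute a harm, but no rate is given, and the per-protocol analysis that would examine this is already planned.

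**Conclusion.** The point stands as a mismatch between the declared hypothesis and the stated test. Non-inferiority is declared in two sections, no margin appears in the protocol, and both the sizing and the description of the primary result belong to a difference test. Followed as written, the plan cannot establish its own hypothesis.

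The stated 97% is arithmetically right, and the same number of children would serve a 5-point margin well. They would not serve a 3-point margin. For the overall comparison at a 5-point deficit, the practical gap between the two approaches is small: 2.3% to 4.6% against 2.5%. These figures rest on SD 40, equal arms and 85% data in each arm. The 5 points are the protocol's detectable difference, used here as a candidate margin that the protocol does not itself justify.

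**What to change.** Before analysis, choose one of two repairs.

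**Keep the non-inferiority label.**

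1. In Sample size considerations, state a margin and justify it as an acceptable loss in mean ASQ score. Five points is the natural candidate because the calculation already uses it, but it must be defended on that ground.
2. In Statistical analysis, state that non-inferiority is concluded if the lower limit of the two-sided 95% CI for the adjusted difference (BCG minus control) lies above minus the margin.
3. Replace the power sentence with non-inferiority power at about 1,700 per arm, using the row of the table above for the chosen margin.
4. Say that the planned per-protocol analysis will be reported in support of the conclusion.

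**Drop the label.** Describe the sub-study as a two-sided estimate of the effect of BCG, reported with its confidence interval. This fits the research question as worded.

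Either repair is a change of wording. With a 5-point margin no extra children or data are needed. A margin of 4 or less would leave power below 90% at the expected response, and the protocol would have to say so.

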# Background

As one of the most used vaccines globally, Bacillus Calmette Guérin (BCG) vaccine is administered in > 100 countries to infants at birth to decrease the incidence of severe tuberculosis. Due to the low incidence of tuberculosis in Denmark, the BCG vaccine was withdrawn from the Danish Child Immunisation Programme in 1982. Recently, studies from West Africa have shown positive non-specific effects of early BCG immunisation on childhood morbidity and mortality (1-10). The studies suggest that BCG immunisation protects against various infectious diseases, such as pneumonia, diarrhoea, meningitis and respiratory syncytial virus (7, 11). Danish children below one year of age have high morbidity, primarily from infectious diseases, and resulting increasing use of primary care services and medication (12). Our group therefore initiated a randomised trial of BCG vaccination with the overall aim to test the hypothesis that the BCG-vaccine has positive nonspecific effects in Danish children.

It may be hypothesised that if BCG immunisation at birth results in a lower burden of disease from infections and less use of medicines, BCG immunised children may have better psychomotor development. To our knowledge it has not previously been addressed whether BCG immunisation at birth affects development. In theory, BCG immunisation at birth may also result in a low grade inflammation that may affect the brain negatively, so assessing this outcome will also address an important safety issue. The overall hypothesis of this sub-study is a non-inferiority of BCG-immunised children relating to development. Assessment of development of preterm infants is already part of the Calmette study protocol.

# Research question

Does BCG immunisation at birth affect development in children in the first year of life?

# Methods

## Overall study

## Inclusion

For 1 year all parents planning to give birth at Rigshospitalet, Hvidovre Hospital and Kolding Hospital will receive at letter during 2^nd^/3^rd^ trimester of pregnancy with information on the study and an invitation to participate in the study. The local PhD-students or research midwifes subsequently call the families. They ask the families whether they are willing to participate in the study. A structured interview with the families will be performed. It will be registered on the medical birth records if the family has consented to participation.

### Exclusion

Infants born before gestational age 32 weeks and/or birth weight < 1000g, infants with known congenital disease, anomaly or malformation, immune deficiency and HIV, will be excluded. Non-Danish speaking parents will be excluded.

*Intervention*

Children born to mothers, who have accepted to participate, will be randomised to either intervention group or to the control group at birth. Block-randomisation stratified by gestational age (≥ 37 weeks of gestation vs. < 37 weeks of gestation) will be performed electronically just before vaccination by the overall study electronic case report system (e-crf).

Vaccination

Children randomised to the BCG vaccination group will receive an intradermal BCG vaccine (Statens Serum Institute “BCG vaccine”) in the standard dose 0.05 ml in the upper, lateral part of the shoulder of the child by specially trained midwives.

### Data collection

At the inclusion and at 3 and 13 months after birth structured telephone interviews will be conducted. These will focus on the infants’ anthropometric measurements, nutrition, visits at the general practitioner, hospitalisations and infectious illnesses. The parents will be invited for clinical examinations of the child at ages 3 and 13 months.

Figure 1 outlines the study design (in Danish).

[figure not shown]

**Emailinvitation til at deltage i børns udvikling sub-studie**

Figure 1: Study design

## Sub-study outcome

Ages and Stages Questionnaire (agesandstages.com): A validated, parent reported questionnaire concerning development in five domains: Communication, gross motor, fine motor, problem solving and social development. The questionnaire results in a combined score (0 - 300) that assesses the overall psychomotor development of the child. The questionnaire will be distributed to all parents of 13 months old children born at term (Appendix 1). Parents will automatically receive an email asking whether they would like to participate in this sub-study when the child is approximately 12.5 months old. The email will contain a link that directs to a web based version of ASQ and parents type the information directly into the electronic case report form.

# Sample size considerations

The overall trial

The main trial includes 4300 children to be able to detect a 20% reduction in infant hospitalisation with 90% power and α = 0.05.

Sub-study

The entire Calmette-cohort will comprise 4300 children. Of these approximately 300 will be preterm (< 37 GA). Based on a sample size of 2000 mature children in each group, an α = 0.05, a mean ASQ score of 200 with a standard deviation (SD) of 40 this study will have a power of approximately 97% to detect a 5 points difference (effect size 0.12) between mean scores in BCG vaccinated children compared to unvaccinated children. When used for screening purposes, an ASQ score of ≥1.5 SD (approximately 60 points at age 13 months) below the mean is considered indication of developmental delay (13). The high power of this sub-study will allow meaningful exploratory subgroup analyses.

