**Sensitivity analyses:**

We expect to have data on approx. 85% of enrolled children. Some of these data may be incomplete. The ASQ manual suggests that partially completed scores can be used to impute the total score. The equation is: total ASQ score = sum of ASQ sub-scores / (300 - 10 * no. of missing)*300. In case of questionnaires less than 66% complete, they will count as missing. Sensitivity analyses using the simple imputation-data will be conducted.

Completely missing scores will be imputed using multiple imputations. Questionnaires less than 66% filled will be set to missing and then imputed.

Excluding children that did not follow the allocation.

**Exploratory outcomes:** Correlation of age-adjusted ASQ sum-score with sum of parent reported illness. Exploratory analyses will be presented with crude p-values not corrected for multiple comparisons.

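### The sub-study's 97% power counts every expected term child, although the protocol expects data on only about 85% of enrolled children; at that response, power is about 95%

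*Protocol*

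**What the plan says.** Under Sample size considerations the protocol starts from the whole cohort ("The entire Calmette-cohort will comprise 4300 children") and sets aside about 300 preterm infants. It then gives power for the sub-study: "Based on a sample size of 2000 mature children in each group", with "a mean ASQ score of 200 with a standard deviation (SD) of 40" and an alpha of 0.05 whose sidedness is not given. The result is power of about 97% for a difference of 5 points, printed as an effect size of 0.12. The same paragraph says this power is high enough to make exploratory subgroup work meaningful.

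Under Sensitivity analyses the protocol says: "We expect to have data on approx. 85% of enrolled children. Some of these data may be incomplete". Multiple imputation of wholly missing scores appears under that same heading.

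Three other places bear on the point. Sub-study outcome sends the questionnaire to parents of children born at term, by an automatic email that asks whether they wish to take part. Adjustment promises all main results overall and separately for girls and boys. Summary and Background describe the sub-study as one of non-inferiority.

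**The concern.** The two sections give different sizes for the same analysis. The power calculation treats 2,000 observed scores per group as given, which requires every invited family to return the web questionnaire. The section on sensitivity analyses expects roughly one child in seven to have no data. Both figures are the protocol's own, so no outside assumption is needed to see the mismatch.

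Two things depend on the number. The first is the precision a reader should expect: in a study framed as non-inferiority, the conclusion rests on the width of the confidence interval. The second is the statement that power is high enough for useful subgroup work, which is drawn directly from the full-response figure.

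**Working it through.** **Inputs.** From Sample size considerations: cohort 4,300, about 300 preterm, 2,000 term children per group, SD 40, difference 5 points, alpha 0.05. From Sensitivity analyses: data on about 85%. Assumed: a two-sided test, because sidedness is not stated, and an even sex split in the last step.

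**Where the 2,000 comes from.** (4,300 − 300)/2 = 2,000. It is the full expected term cohort, with nothing taken off for non-response.

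**Formulas.** SE = SD × √(2/n). Power = Φ(difference/SE − 1.96). Half-width of the 95% confidence interval = 1.96 × SE.

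**The plan's own figure.** With n = 2,000, SE = 40 × √(2/2000) = 1.265. Power = Φ(5/1.265 − 1.96) = Φ(1.99) = 97.7%. Taking the printed effect size of 0.12 literally (0.12 × 40 = 4.8 points) gives 96.7%. Either fits the stated 97%, so the figure reproduces, with a two-sided test and no loss. A one-sided alpha of 0.05 would give 99.0% and 98.4%, a poorer fit.

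**At 85% response, term children.** n = 0.85 × 2,000 = 1,700. SE = 40 × √(2/1700) = 1.372. Power = Φ(5/1.372 − 1.96) = Φ(1.68) = 95.4%.

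**At 85% of the whole cohort, preterm included.** n = 0.85 × 4,300/2 = 1,827.5, taken as 1,827. Power = 96.5%.

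| Observed per group | Power, 5 points | Power, effect size 0.12 | 95% CI half-width | Difference detectable with 97% power |
|---|---|---|---|---|
| 2,000 | 97.7% | 96.7% | 2.48 | 4.86 |
| 1,827 | 96.5% | 95.2% | 2.59 | 4.94 + 0.14 = 5.08 |
| 1,700 | 95.4% | 93.8% | 2.69 | 5.27 |

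The last column is (1.96 + 1.881) × SE; for 1,827, SE = 1.323 and the product is 5.08. For 97% power at 5 points, 1,889 observed scores per group are needed.

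**By sex, assuming an even split.**
- Full response, n = 1,000: SE = 1.789, power = Φ(5/1.789 − 1.96) = 79.8%.
- 85% response, n = 850: SE = 1.940, power = Φ(5/1.940 − 1.96) = 73.1%.

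**The case against.** The strongest reply is that nothing is miscalculated and little follows. The 97% is correct for the inputs printed beside it, and 95.4% is only 1.6 points below a figure given as approximate. The half-width grows by about 0.2 points on a 0–300 scale, where the protocol places the screening threshold for delay some 60 points below the mean. Enrolment is set by the main trial's hospitalisation endpoint, so the sub-study could not change it in any case. All of this stands, and it is why the point is minor.

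The 1,700 is also not the only reading. The 85% refers to enrolled children, and prematurity is both a covariate in the planned regression and a planned subgroup, so preterm children may be analysed. Power would then be 96.5%, hard to tell from the stated figure. The term-only distribution of the questionnaire, and a power calculation confined to term children, make 1,700 the more consistent reading, but the protocol does not settle it.

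Sidedness matters too. With a one-sided alpha of 0.05, 1,700 per group gives Φ(5/1.372 − 1.645) = 97.7% and there is no shortfall against 97%. The printed figure fits a two-sided test better, but that is an inference.

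On the results by sex, most of the fall comes from splitting the cohort (97.7% to 79.8%), not from non-response (79.8% to 73.1%), and the protocol calls its subgroup analyses exploratory. That is fair, but the results for girls and boys are promised for all main results, and neither figure matches the high power on which the subgroup sentence relies.

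One might answer that multiple imputation restores the 2,000. It does not: it is listed as a sensitivity analysis, and imputing 300 unobserved scores per group does not supply the information that observing them would.

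**Conclusion.** A minor inconsistency that should be reconciled. The sample size section assumes complete response and the section on sensitivity analyses expects about 85%. On the more consistent reading, power for a 5-point difference is about 95% and the half-width about 2.7 points, instead of 97% and 2.5. On the alternative reading, power is about 96.5%. These figures rest on SD 40, equal groups and a two-sided alpha of 0.05. The results by sex, at about 73% under an even split, are where the difference is of practical note.

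A reader might infer three stronger things that the protocol does not support:
- **That the 97% is an arithmetic error.** It reproduces from its stated inputs.
- **That the sub-study is underpowered.** Overall power stays above 90% on either reading of the 85%.
- **That the observed sample is smaller still because some returned forms will be incomplete.** The protocol gives no rate for this. An assumed 10% of unusable forms would leave 1,700 × 0.9 = 1,530 per group and about 93.3% power, but that 10% is purely illustrative.

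**What to change.** In Sample size considerations, restate the sub-study calculation for the number expected to be observed: with about 85% response, about 1,700 term children per group give about 95% power for a 5-point difference (SD 40, two-sided alpha 0.05, if that is what is intended), with a 95% confidence interval half-width of about 2.7 points. State the sidedness of alpha explicitly. Say whether the 85% refers to term children or to all enrolled children; if preterm children are included, give the corresponding figure (about 1,827 per group, about 96.5%).

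Qualify the subgroup sentence by giving the power for the results by sex, about 73% for 5 points with 850 per group under an even split, rather than relying on the overall figure.

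The cost is a slightly less favourable stated power. Enrolment, design and analysis stay as they are.
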